##### Intervention description {11a}

When the decision is made by the obstetrician to perform an emergency caesarean section (delay <15 min), the anesthesiologist immediately proceeds to inject the epidural catheter with either:20 ml of 2% lidocaine with epinephrine 1:200,000 or12 ml of a mixture of 10 mL 2% lidocaine with epinephrine 1:200,000 plus 2 mL 4.2% sodium bicarbonate

##### Criteria for discontinuing or modifying allocated interventions {11b}

The experimental procedure in this clinical trial involves injecting a different type and volume of local anesthetic than the control group. This injection is given shortly after the participant’s study inclusion and randomization and is a one-time dose, meaning that the treatment cannot be interrupted. There is no specific experimental protocol to follow after this injection. Instead, the usual medical practices for administering an epidural injection of lidocaine for emergency caesarean section will be followed, and data will be collected.

##### Strategies to improve adherence to interventions {11c}

In order to assure that the correct concentrations and volumes of local anesthetic are administered, the syringes containing either lidocaine with epinephrine (LE) or lidocaine with epinephrine plus bicarbonate (LEB) will be prepared beforehand and stored in a refrigerator near the delivery room for a 24-h period. After the patient’s inclusion in the study, the investigators will have simply to epidurally inject the contents of the prepared syringe that correspond to the group to which the patient has been assigned.

##### Relevant concomitant care permitted or prohibited during the trial {11d}

Before inclusion in the study, the maintenance of epidural analgesia will be ensured by continuous infusion of a mixture of levobupivacaine 1.225% or ropivacaine 1%, combined with sufentanil 0.25 μg/ml delivered through patient-controlled epidural analgesia (PCEA). The management of additional bolus doses of analgesia, if required, will be left to the discretion of the managing anesthesiologist. Obstetrical labor monitoring will be performed in line with current standard of care.

After study inclusion and the injection of the bolus dose of LE or LEB, additional analgesic treatments can be used at the discretion of the managing anesthetist, within the limits of compliance with the main evaluation criterion: the conversion to general anesthesia in the event of pain evaluated at more than 3/10 on the visual numerical scale.

### Provisions for post-trial care {30}

The sponsor and the investigator(s) undertake that this research will be carried out in accordance with the law n°2012-300 of March 5, 2012, relating to research involving the human person, as well as in accordance with the Good Clinical Practices and the Declaration of Helsinki (which can be found in its complete version on the site http://www.wma.net).

The Bordeaux University Hospital, promoter of this research, has taken out a civil liability insurance policy with LLOYD’S INSURANCE COMPANY SA, through the brokerage firm BEAH SAS, in accordance with the public health code.

### Outcomes {12}

Primary outcome:Rate of conversion to maternal general anesthesia for insufficient analgesia (defined as the intravenous injection of general anesthetic agents and the need for orotracheal intubation) between the time of the injection of a bolus dose of LE or LEB and clamping of the umbilical cord.

Secondary outcomes:Time from the decision to extract the fetus by emergency caesarean section (caesarean decision) to the birth of the baby (the number of minutes from caesarean decision to the clamping of the umbilical cord).Time from caesarean decision to incision (the number of minutes from caesarean decision to surgical incision)Incidence of maternal complications after the injection of an anesthetic dose of LE or LEB, and in particular that of intraoperative and postoperative nausea or vomiting, arterial oxygen desaturation (SpO2 < 94%), difficult intubation (> 2 direct laryngoscopies), aspiration of gastric contents and/or aspiration pneumonitis, arterial hypotension prior to fetal extraction (MAP < 65 mmHg), extensive sensory or motor block (level ≥ C8)Use of adjunct medications necessary for maternal comfort during caesarean sectionPostpartum hemorrhage (bleeding > 500 mL)Pediatric wellness criteria (cord pH < 7; cord lactate levels)Level of anesthesia assessed 1 h after surgical incisionMaternal satisfaction with analgesia and anesthesia during caesarean section.

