### Objectives {7}

Based on the results of the preliminary audit, we plan to conduct the QETAL study. This bicentric, randomized controlled patient-blinded clinical trial will focus on parturients who have an epidural catheter in place for labor analgesia and require emergent fetal extraction (<15 min). Our hypothesis is that adding sodium bicarbonate to the lidocaine-epinephrine solution administered through the epidural catheter will reduce the rate of conversion to general anesthesia due to faster onset of surgical epidural anesthesia.

General anesthesia in this context is defined as intravenous induction of general anesthesia and tracheal intubation between the attempted conversion of epidural analgesia to surgical anesthesia via the epidural catheter and umbilical cord clamping. The primary objective is to evaluate whether alkalinization of lidocaine decreases the need for conversion to general anesthesia. Secondary objectives include comparing the delay to maternal incision and fetal extraction, maternal and fetal safety criteria, the level of anesthesia assessed 1 h after surgical incision, and maternal satisfaction with analgesia and anesthesia between the two groups.

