### Sample size {14}

No previous study has investigated the use of general anesthesia after epidural extension with an alkalinized local anesthetic solution in extremely emergency caesarean sections during labor. However, a preliminary retrospective clinical audit conducted in 2019 at the Bordeaux University Hospital maternity ward found that the rate of recourse to general anesthesia was 100% (4 out of 4) in the lidocaine alone group, versus 0% (0/7) in the lidocaine-bicarbonate group. Although the sample size was small, the difference was significant (*p*=0.003). Therefore, caution should be exercised when using this preliminary result to calculate the number of subjects required for the current trial. Conservatively, assuming a general anesthesia conversion rate of 80% in the control group and 40% in the experimental group, 44 patients will be required in the lidocaine-bicarbonate group and 22 patients in the lidocaine group, for a total of 66 patients in a 2:1 ratio. The number of subjects required was calculated for a two-sided comparison test of two proportions with a 90% power and a 5% risk alpha.

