## Assignment of interventions: allocation

### Sequence generation {16a}

The randomization list will be established by the statistician of the Clinical Epidemiology Unit of the Bordeaux University Hospital before beginning the study. The 2 treatment groups will be unbalanced with a 2:1 ratio in favor of the experimental group (44 subjects in the LEB group and 22 subjects in the LE group). Randomization will be stratified by the investigating center. A document describing the randomization procedure will be kept confidential in the Clinical Epidemiology Unit.

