## Statistical methods

### Statistical methods for primary and secondary outcomes {20a}

The primary statistical analysis will compare the proportion of general anesthesia use between groups LEB and LE. The two groups will be compared using a chi-squared test, a corrected chi-squared test, or a Fisher’s exact test depending on the distribution of the theoretical numbers under the assumption of independence. The two-sided 95% confidence interval will be estimated for each group according to the exact binomial distribution.

Secondary outcomes will be compared according to the following principles. Quantitative variables will be compared by Student’s *t* test, Student’s test for unequal variances, or a non-parametric Wilcoxon test depending on the conditions of application of these tests. Linear regression models will be used to adjust for the major confounders. The assumptions of the model (normality and homoscedasticity of the residuals, linearity of the association for the quantitative factors) will be systematically verified. A transformation of the criteria may be envisaged in the event of deviation from the models’ hypotheses.

Qualitative variables will be compared by a chi-squared test, a corrected chi-squared test, or a Fisher’s exact test according to the distribution of the theoretical numbers under the hypothesis of independence. Logistic regression models will be used to adjust for the major confounders. The hypothesis of the models (log-linearity of the association for the quantitative factors) will be systematically tested.

A graphical representation will be associated as much as possible with the analyses

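### Cord pH is listed as a secondary outcome only as pH < 7, which will probably give few events in 66 births; listing the measured value as well would cost almost nothing

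*Protocol article*

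**What the plan says.** In the protocol article, Outcomes {12} has one item on the newborn's condition, whose content is given in brackets as "cord pH < 7; cord lactate levels". Lactate has no cut-off. Cord pH is named only through the cut-off, and no other section of the article names it as a quantity.

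Statistical methods {20a} sets rules by type of variable. For binary items, "Qualitative variables will be compared by a chi-squared test", its corrected form or Fisher's exact test, with logistic regression for adjustment. Quantitative items go to a t test, an unequal-variance t test or a Wilcoxon test, with linear regression for adjustment. Read together, the two sections send pH < 7 to the first set and lactate to the second.

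Objectives {7} includes "maternal and fetal safety criteria" among several secondary objectives and ranks none of them. The trial is sized for general anesthesia alone (Sample size {14}), with "44 subjects in the LEB group and 22 subjects in the LE group" (Sequence generation {16a}).

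**The concern.** A pH has to be measured before it can be called below 7. Reducing the measurement to a yes/no event discards most of what it says about a shift between arms, and the loss is greatest when the event is rare. The article gives no reason for handling pH and lactate differently within one item.

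A neonatal effect in either direction is of interest. The arms differ in solution and volume, the plan expects a large difference in general anesthesia, and the Background links general anesthesia to neonatal respiratory depression. With very few events, the pH < 7 comparison could miss a sizeable shift either way, and a non-significant result would say little about neonatal safety.

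**Working it through.** **The plan's own figure.** Inputs from Sample size {14}: "general anesthesia conversion rate of 80% in the control group and 40% in the experimental group", and a "two-sided comparison test of two proportions with a 90% power and a 5% risk alpha", allocated 2:1.

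- Pooled proportion: (0.80 + 2 × 0.40)/3 = 0.533.
- LE arm: n = [1.960 × √(0.533 × 0.467 × 1.5) + 1.282 × √(0.80 × 0.20 + 0.40 × 0.60/2)]² / 0.40² = 21.99, so 22.
- LEB arm: 44. Total 66, as stated.

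The arm sizes used below are therefore sound.

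**Without any assumed rate.** Two-sided Fisher test at 22 vs 44:

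- No event in LE: 7/44 in LEB gives p = 0.086 and 8/44 gives p = 0.045. LEB needs at least 8/44 (18%).
- No event in LEB: 2/22 in LE gives p = 0.108 and 3/22 gives p = 0.034. LE needs at least 3/22 (14%).
- Zero events in an arm: the upper limit of the exact two-sided 95% interval is 1 − 0.025^(1/n), which is 15.4% for n = 22 and 8.0% for n = 44.

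**Expected counts.** The article gives no rate of pH < 7, so a range is assumed. If both arms share rate p, the expected events are 66p and the chance of none is (1 − p)^66.

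| Assumed p | Expected events in 66 | Chance of no event |
|---|---|---|
| 1% | 0.66 | 52% |
| 2% | 1.3 | 26% |
| 5% | 3.3 | 3% |
| 10% | 6.6 | 0.1% |

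**Power for one shift, read two ways.** Assume normally distributed pH with equal SD, rate p in the better arm, and a 0.75 SD downward shift in the other. The worse arm's rate is Φ(Φ⁻¹(p) + 0.75); for p = 2%, Φ(−2.054 + 0.75) = 9.6%. Fisher power is the summed probability of all tables at 22 vs 44 with two-sided p ≤ 0.05.

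| Rate in better arm | Rate in worse arm | Fisher power, LEB worse | Fisher power, LE worse |
|---|---|---|---|
| 1% | 5.7% | 0.3% | 9% |
| 2% | 9.6% | 4% | 21% |
| 5% | 18.5% | 26% | 37% |
| 10% | 29.8% | 41% | 43% |

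**Comparing mean pH in the same births.** Two-sided t test, 64 degrees of freedom, noncentrality d/√(1/22 + 1/44) = d/0.261:

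- d = 0.75: noncentrality 2.87, power 81%.
- d = 0.50: noncentrality 1.91, power 47%.
- d = 0.25: noncentrality 0.96, power 16%.
- 80% power is reached at about d = 0.74.

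Across the assumed range, the threshold comparison has at most about half the power of the mean comparison for the 0.75 SD shift (43% against 81%). At 2% or below with LEB worse it has almost none.

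**The case against.** **The neonatal comparison is not empty.** Cord lactate stands in the same item with no cut-off, and a quantitative test on it at 22 vs 44 has the same power per SD as a test on mean pH. This stands. A reader might infer that the main neonatal safety comparison is left with almost no information, but the article ranks no neonatal outcome and keeps lactate as a level. The point concerns pH alone.

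**The analysis of pH is inferred.** {20a} gives rules by variable type and never assigns cord pH to a test. An analysis plan not shown here could add the continuous value. This stands in part: the article does not rule out such an analysis. The cut-off, however, is in the outcome definition itself, so analysing the value would go beyond the outcome as published.

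**A threshold can be a legitimate safety definition.** Other items use one too (SpO2, MAP, blood loss). This stands, and is why pH < 7 should stay a listed outcome.

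**The size rests on assumptions.** Event rate, normality and shift are all assumed, and 0.75 SD lies almost at the point where the mean comparison reaches 80% power. This also stands. At 0.5 SD even the mean comparison has less than half a chance, so listing the value would not secure detection of moderate harm. At 5% to 10%, the threshold comparison is weak rather than void.

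**False reassurance.** A reader might infer that the plan would take a non-significant pH < 7 result as evidence of safety. No section says so or claims equivalence or non-inferiority; the risk lies in how a reader might take the result.

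**Conclusion.** The point holds as a minor one. Cord pH is defined as an outcome only through pH < 7, and at 22 vs 44 that definition gives much less power than the measured value would. The 8/44 requirement when LE has no event needs no assumed rate. The power contrast (4% to 43% for the threshold against about 81% for the mean) rests on an assumed 2% to 10% of births below 7 in the better arm, normally distributed pH with equal SD, a 0.75 SD shift and Fisher's test throughout. The primary outcome and the sample size are unaffected.

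**What to change.** In Outcomes {12}, list cord pH also as a continuous secondary outcome beside lactate. Report the mean difference with its 95% confidence interval, using the quantitative methods already in {20a}. Keep pH < 7 as a listed outcome, with the count in each arm and exact confidence intervals, so that a small number of events is shown with its uncertainty.

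The cost is a change of wording, with no extra patients or procedures, provided the numeric pH is recorded when it is classified. The data collection form is not shown here, so the sponsor should confirm this. The text should not suggest that the addition gives adequate power for moderate shifts.

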### Participant timeline {13}

Patients will receive written information about the QETAL study during the preoperative anesthesia consultation. Upon admission to the delivery room, the anesthesiologist will review the study information again with the patient (see Fig. 1 and Table 2). Epidural analgesia will then be administered according to departmental protocols. Once the decision is made that emergent fetal extraction (>15 min) will be required, the patient will be randomized to either the LE or LEB treatment arm. Because it is impossible to equalize the volume of the injected solution into the epidural space between groups without affecting the level of anesthesia obtained, the control group will receive two 10-mL syringes, totaling 20 mL, while the experimental group will receive a single 12-mL syringe. As a result, it is not possible to use concealed syringes in a way that would allow the administering physician to be unaware of the solution they are injecting or the group to which the patient has been randomized. Consequently, the involvement of two anesthesiologists is necessary. The anesthesiologist who performs the epidural conversion will be designated as “Investigator A” and may delegate this injection to an authorized person. The patient will then be transferred to the operating room for the caesarean section, where the surgical anesthesia quality will be evaluated by the operating obstetrician in the presence of a second anesthesiologist (“Investigator B”). At no point will "Investigator A" communicate the nature or quantity of the solution used for the epidural injection to "Investigator B". Finally, the patient's written consent will be obtained in the recovery room after the procedure.

**Fig. 1 Fig1:**
[figure not shown]
Patients will be informed about the study before receiving epidural analgesia and randomized to one of two treatment arms if emergent fetal extraction is required. The anesthesiologist administering the epidural conversion will be considered “Investigator A,” and the quality of surgical anesthesia will be evaluated by a second anesthesiologist (“Investigator B”). The patient’s written consent will be obtained in the recovery room after the procedure

**Table 2 Tab2:**
[figure not shown]
Timing of participant recruitment, administration of interventions, and collection of data

*OR* Operating room, *PACU* Post-anesthesia care unit

### Sample size {14}

No previous study has investigated the use of general anesthesia after epidural extension with an alkalinized local anesthetic solution in extremely emergency caesarean sections during labor. However, a preliminary retrospective clinical audit conducted in 2019 at the Bordeaux University Hospital maternity ward found that the rate of recourse to general anesthesia was 100% (4 out of 4) in the lidocaine alone group, versus 0% (0/7) in the lidocaine-bicarbonate group. Although the sample size was small, the difference was significant (*p*=0.003). Therefore, caution should be exercised when using this preliminary result to calculate the number of subjects required for the current trial. Conservatively, assuming a general anesthesia conversion rate of 80% in the control group and 40% in the experimental group, 44 patients will be required in the lidocaine-bicarbonate group and 22 patients in the lidocaine group, for a total of 66 patients in a 2:1 ratio. The number of subjects required was calculated for a two-sided comparison test of two proportions with a 90% power and a 5% risk alpha.

### Recruitment {15}

Each center will recruit as many patients meeting the eligibility criteria as needed, up to 66 patients.

## Assignment of interventions: allocation

### Sequence generation {16a}

The randomization list will be established by the statistician of the Clinical Epidemiology Unit of the Bordeaux University Hospital before beginning the study. The 2 treatment groups will be unbalanced with a 2:1 ratio in favor of the experimental group (44 subjects in the LEB group and 22 subjects in the LE group). Randomization will be stratified by the investigating center. A document describing the randomization procedure will be kept confidential in the Clinical Epidemiology Unit.

### Concealment mechanism {16b}

To ensure the concealment of the treatment allocation in this randomized study, a web-based system cannot be used due to the extreme emergency of the anesthetic procedure. Therefore, the randomization process will be conducted in advance during the preparation of the refrigerated syringes. The randomization list will be securely stored in a sealed envelope in the birthing room of the investigating centers, accessible only by the nurse anesthetists who are responsible for syringe preparation. This method will ensure that the treatment allocation remains concealed until the point of injection, preventing any potential bias in the study.

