### Implementation {16c}

To ensure efficient and accurate randomization, three syringes will be prepared per 24 h. The syringes will be labeled with patient numbers (patient 1, patient 2, or patient 3) based on their corresponding rank in the randomization list for that period. The solutions in the syringes will be identified by batch numbers, and the information of the patient to whom the syringe is dispensed will be recorded along with the date of injection. The syringes will be stored in a secure refrigerator in the delivery room for a maximum of 24 h. Unused syringes will be discarded after 24 h, and the randomization numbers for the unused syringes will be recycled for the following day’s preparations. This method ensures that the randomization process remains confidential and secure.

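### The assurance that allocation stays concealed until injection is not supported by the procedure described: visibly different, rank-labelled sets stand ready in the delivery room before eligibility is checked

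*Protocol article*

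**What the plan says.** Under Concealment mechanism {16b}, web randomization is ruled out because of the urgency. The list is instead kept in a sealed envelope in each birthing room, "accessible only by the nurse anesthetists who are responsible for syringe preparation". The section concludes: "This method will ensure that the treatment allocation remains concealed until the point of injection", and presents this as preventing bias.

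Under Implementation {16c}, treatments are prepared in advance, three each day: "The syringes will be labeled with patient numbers (patient 1, patient 2, or patient 3) based on their corresponding rank in the randomization list". They are "stored in a secure refrigerator in the delivery room for a maximum of 24 h". What is not used is discarded, and "the randomization numbers for the unused syringes will be recycled for the following day".

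Under Participant timeline {13}, "the control group will receive two 10-mL syringes, totaling 20 mL, while the experimental group will receive a single 12-mL syringe", and for that reason "it is not possible to use concealed syringes in a way that would allow the administering physician to be unaware of the solution". Who will be blinded {17a} confirms that the injecting anaesthesiologist (Investigator A) knows the arm, while Investigator B and the obstetrician do not. The Discussion says that eligibility is checked before a labelled product is used, which is after it has been prepared.

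**The concern.** Concealment of allocation and blinding are separate safeguards. Blinding protects treatment and outcome assessment after inclusion. Concealment protects the decision to include. If someone involved in that decision can know which arm comes next, the two groups may differ in risk before any drug is given. A blinded operating-room team cannot correct that, and analysis cannot recover women who were passed over without a record.

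The protocol gives reasons to take this seriously. By its Background, practitioners in the unit already choose between these two mixtures in routine care. By its Discussion, the team expects the bicarbonate arm to do better. A woman left out of the trial can still receive either mixture. Since the person injecting is unblinded by design, concealment before inclusion carries much of the protection of the primary comparison.

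**Working it through.** **1. The plan's own figure.** Sample size {14} assumes 80% versus 40%, two-sided 5%, 90% power and 2:1 allocation. The pooled rate is (0.8 + 2 × 0.4)/3 = 0.533. Control n = [1.960 × √(0.533 × 0.467 × 1.5) + 1.282 × √(0.8 × 0.2 + 0.4 × 0.6/2)]² / 0.4² = (1.198 + 0.678)²/0.16 ≈ 22, so 22 + 44 = 66. The stated number reproduces. Nothing in this point changes it.

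**2. The sections side by side.**

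| Needed for concealment until injection | What the article describes |
|---|---|
| Sets look alike before inclusion | Two 10-mL syringes versus one 12-mL syringe ({13}); no outer packaging described |
| Next rank not identifiable | Labelled patient 1, 2 or 3 by list rank ({16c}) |
| Set out of sight until inclusion | In a delivery-room refrigerator for up to 24 h ({16c}) |
| Eligibility settled before the arm is knowable | Eligibility checked after preparation (Discussion) |
| List away from those who enrol | List on site, used by the preparing nurses ({16b}); nothing described keeps them or Investigator A out of the inclusion decision |

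**3. How long one allocation may stand ready.** Recruitment began on 7 July 2022 and was to finish in Q3 or Q4 2023 (Trial status), that is, between 1 July and 31 December 2023: 359 to 542 days. For 66 women this is 359/66 = 5.4 to 542/66 = 8.2 days per inclusion overall. With an equal split, 33 per centre (an assumption; Recruitment {15} sets no quota), it is 359/33 = 10.9 to 542/33 = 16.4 days. Because unused numbers are recycled, the same next arm would be prepared again each day over that interval, on average.

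**4. Illustration of size.** The inputs are assumed, not taken from the documents. There is no true effect. Half of candidates have a 40% risk of general anaesthesia and half 80%. A share s of high-risk women is kept out when LEB is next, and the same share of low-risk women is kept out when LE is next.

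LEB rate = [0.4 + 0.8(1 − s)]/(2 − s); LE rate = [0.8 + 0.4(1 − s)]/(2 − s).

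The rejection probability is exact (binomial) for 44 versus 22 at two-sided 5%, using the planned rule: Pearson chi-squared if all expected counts are at least 5, otherwise the corrected or Fisher test.

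| s | LEB | LE | Gap (points) | Rejects |
|---|---|---|---|---|
| 0 | 60.0% | 60.0% | 0 | 4.9% |
| 10% | 58.9% | 61.1% | 2.1 | 5.0% |
| 20% | 57.8% | 62.2% | 4.4 | 5.9% |
| 30% | 56.5% | 63.5% | 7.1 | 7.7% |
| 50% | 53.3% | 66.7% | 13.3 | 16.4% |

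This shows one direction only. A clinician who prefers LEB might instead keep a high-risk woman out when LE is next and give LEB outside the trial. LE would then hold lower-risk women, and the bias would run against LEB.

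**The case against.** The other side has several good points.

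- **Access.** The refrigerator is described as secure and the list as sealed and restricted to preparers. A reader might infer that anyone in the unit can read off the next arm, or that the list lies open after the first preparation. The article says neither: access to the refrigerator is not specified, and resealing is not addressed.
- **Packaging.** The statement in {13} that syringes cannot be concealed concerns the person injecting, at injection. It does not exclude an opaque outer box beforehand. Sequence generation {16a} mentions a separate confidential document on randomization, which may describe one. The point is therefore conditional on there being no such packaging.
- **Urgency.** It is tempting to count the under-15-minute label as something that can be steered. That decision belongs to the obstetrician (Intervention description {11a}), who is blinded ({17a}), so it does not count. What remains is the judgement that the epidural is functional, the language barrier, and oral consent. Even there the room is limited: information is given and understanding is checked before catheter placement, and the criteria were deliberately kept few.
- **Size.** Mild steering barely moves the error rate. Even 30% steering gives a gap of about 7 points, against a planned difference of 40.
- **A partial check exists.** The Discussion plans to compare pre-injection sensory levels between arms. That could reveal an imbalance in one important factor, although not in others, and it would not cure it.

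These limit the point but do not remove it. The article makes a positive claim of concealment, and its other sections do not support that claim.

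**Conclusion.** The point holds as a mismatch between an assurance and the procedure described. Unless undescribed packaging hides the sets, staff with access to the refrigerator can know the next arm before inclusion, possibly for 11 to 16 days per centre on an equal split. The blinded operating-room team does not address this.

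A reader might go further and infer that inclusion was steered, or that the result is biased towards LEB. The documents do not support either inference: steering is a possibility, and its direction is open. The rejection rates of 4.9% to 16.4% rest on an assumed risk mix, assumed steering shares and one direction of bias. They show scale and do not predict. Because concealment is what makes 44 and 22 women comparable, and the remedy is cheap, it should be corrected for the inclusions still to come.

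**What to change.** For the remaining inclusions:

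- Pack each number's full set in an identical, opaque, sealed, sequentially numbered box. Open it only once eligibility and oral consent are confirmed. A time mark or verbal confirmation is enough, with the form completed afterwards, so that the injection is not delayed.
- Replace the full on-site list with one opaque numbered envelope per rank, opened at preparation.
- Where existing staffing allows, have preparers take no part in the inclusion decision.
- Log eligible women who were not included, with the reason.
- Delete or qualify the assurance in {16b}, and report the procedure used so far. If opaque packaging is already in use, say so there.

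The cost is boxes, seals and envelopes, and a few seconds to open a box. The sample size remains 66. Unequal injected volumes do not stand in the way, since the box need only hide the set until inclusion.
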